### Intervention

#### Intervention group

A complex intervention with two phases is conducted:First phase: FP training. This will consist of a previously designed training activity, delivered using the massive online open courses (MOOC) format, including basic concepts relating to multimorbidity, appropriateness of prescribing, treatment adherence, the Ariadne principles, and physician-patient shared decision making.Second phase: Physician-patient interview based on the Ariadne principles.

This intervention has been developed in accordance with the recommendations and taxonomy proposed by the Cochrane Effective Practice and Organisation of Care Review Group (EPOC). The intervention is described in detail in Fig. 2, following the approach proposed by Perera et al. [36].

**Fig. 2 Fig2:**
[figure not shown]
Complex intervention pat plot. *QoL* quality of life, *MOOC* Massive Online Open Courses

#### Control group

Patients in the control group will receive usual clinical care based on the provision of advice and information and will undergo examinations as recommended in the CPGs corresponding to each of the patient’s chronic diseases.

### Variables

FPs will provide their data before the start of the study. Patient data will be collected by the recruiting FP, who will also be responsible for patient follow-up. All information will be recorded in a case report form designed for the study. Each FP will access the form from his/her personal computer via the project website using a personal identification code. Three visits are defined for patient data collection: baseline (T0), 6 months (T1), and 12 months (T2) (see Table 1).

**Table 1 Tab1:** Visit plan

	T0 (baseline)		T1 (6 months)	T2 (12 months)	Responsible entity
Confirm inclusion/exclusion criteria	X				FP
Written informed consent	X				FP
Socio-demographic variables	X				FP
Morbidity variables and drug treatment plan	X		X	X	FP
Randomization of FPs		X			RU
FP intervention (intervention group)		X			RT
Patient intervention (intervention group)		X	X		FP
Use of health services	X		X	X	RT
Medication adherence	X		X	X	FP
Medication safety			X	X	FP
Quality of life	X		X	X	FP
Costs				X	RT
MAI	X		X	X	EE EC

*FP* family physician, *RU* research unit, *RT* research team, *EE* external evaluator, *EC* evaluation committee, *MAI* medication appropriateness index

#### Primary outcome

Appropriateness of prescription will be measured by the medication appropriateness index (MAI). The main outcome variable will be evaluated by an independent FP with training in the MAI. To ensure consistent ratings, an analysis of intra-observer and inter-observer reliability of evaluators will be conducted. Additionally, a FP and a pharmacist will conduct a second appraisal of the inter-observer reliability over a randomly selected 10% of the completed questionnaires. This measure has been proposed in other studies using the MAI [37].

#### Secondary outcomes

Use of health services: unplanned and/or avoidable hospitalizations, use of emergency services and PC (FP and nurse).Quality of life: measured using the EuroQol 5D-5L questionnaire [38, 39].Medication safety: measured as the incidence of adverse drug reactions and potentially hazardous interactions, classified using the taxonomy proposed by Otero-López [40].Treatment adherence: measured using the Morisky-Green test [41] and the Haynes-Sackett questionnaire [42].Patient perception of shared decision making: measured using a single, multiple choice question, formulated ad hoc.Cost-utility: time spent on training FPs, cost of teaching staff, time spent on physician-patient interviews, utilities measured using the EuroQol 5D-5L.

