The sharing of common and realistic treatment goals between physician and patient is essential to tackle multimorbidity in the PC context and is the cornerstone of the Ariadne principles [28]. The implementation of these principles is based on a thorough assessment of the diseases, treatments and potential treatment interactions, global clinical status, and context of the patient by the physician. This allows prioritization of patients’ health problems, taking into account their preferences and wishes and ensuring their individualized management and monitoring. Despite numerous studies demonstrating the effectiveness of shared decision making on health outcomes [29–31], the feasibility of implementation and the impact of the Ariadne principles in PC have not been assessed to date, although the potential benefit of implementing such a strategy in routine clinical practice has been recognized [32, 33].

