#### Secondary

To evaluate the effects of the complex intervention on medication appropriateness after 12 months (T2), as well as on the use of health services, patient quality of life, treatment adherence, and medication safety, as compared with usual care.To study the cost-utility ratio of the intervention as compared with that of usual care.

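### Medication safety is recorded by the unmasked treating physician, and only one arm is trained and directed towards interactions, so ascertainment can differ between arms

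*Protocol article*

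**What the plan says.** All references are to the protocol article.

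- **Objective.** Objectives, Secondary lists "treatment adherence, and medication safety, as compared with usual care", so safety is a between-arm comparison.
- **Definition.** Secondary outcomes defines it as "measured as the incidence of adverse drug reactions and potentially hazardous interactions", classified by a cited taxonomy.
- **Who records it, and when.** Under Variables: "Patient data will be collected by the recruiting FP, who will also be responsible for patient follow-up". In Table 1 the row "Medication safety" is marked at T1 (6 months) and T2 (12 months), not at T0, with the FP as responsible entity.
- **What only one arm receives.** The training described under Intervention group is an online course "including basic concepts relating to multimorbidity, appropriateness of prescribing, treatment adherence, the Ariadne principles, and physician-patient shared decision making". By the Discussion, control FPs are offered it only after the intervention has ended. The Table 1 row "Patient intervention (intervention group" is marked between T0 and T1 and again at T1. The Background says that the principles behind the interview rest on a "thorough assessment of the diseases, treatments and potential treatment interactions", along with clinical status and context. Controls receive usual care.
- **Masking.** The Discussion says that the intervention cannot be masked, and that outcomes are evaluated by FPs and pharmacists who do not know the allocation. Table 1 names the external evaluator and evaluation committee in the MAI row only.

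**The concern.** A count of safety events is a count of what someone found and wrote down. Here the finder is the treating FP, who knows the allocation. In one arm that FP has been trained in appropriate prescribing and told to consider interactions between treatments, and interactions are one of the two things counted. An interaction present equally often in both arms may then be recorded more often in the intervention arm. The T1 mark adds to this: intervention activity and the first safety recording fall at the same visit, in one arm only.

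At stake is the secondary safety objective. A real benefit could be hidden, or a neutral intervention could look harmful. With no safety value at T0, a difference in recording could not be seen against a common starting point.

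**Working it through.** **Step 1. What the visit plan fixes.** Table 1, side by side:

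| | Intervention arm | Control arm |
|---|---|---|
| FP training before outcomes | yes | no |
| Patient intervention between T0 and T1 | yes | no |
| Patient intervention at T1 | yes | no |
| Safety recorded at T0 | no | no |
| Safety recorded at T1 and T2 | yes, by the FP | yes, by the FP |
| Drug treatment plan recorded at T0, T1, T2 | yes | yes |

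Scheduled safety recording is two visits against two. What differs is the recorder's training, the intervening interview and the intervention activity at T1.

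**Step 2. Overlap with the outcome.** The outcome has two parts. For interactions the overlap is in the text: the Background names them as something the FP assesses. For adverse reactions it is inferred: neither the Background sentence nor the list of training topics mentions detecting reactions, although a closer look at a patient's treatment plausibly brings some to light.

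**Step 3. What unequal detection would do.** The article gives no event rate and no detection probability, so there is no plan figure to reproduce for this outcome; its sample size concerns the MAI. All detection values below are assumptions. Ignoring false positives,

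recorded risk = true risk × detection probability, so recorded RR = true RR × (detection in intervention ÷ detection in control).

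| True RR | Detection, control | Detection, intervention | Recorded RR |
|---|---|---|---|
| 1.00 | 60% | 67% | 0.67/0.60 = 1.12 |
| 1.00 | 60% | 75% | 0.75/0.60 = 1.25 |
| 1.00 | 70% | 90% | 0.90/0.70 = 1.29 |
| 1.00 | 50% | 80% | 0.80/0.50 = 1.60 |
| 1.00 | 70% | 60% | 0.60/0.70 = 0.86 |
| 0.80 | 60% | 75% | 0.80 × 1.25 = 1.00 |

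**Step 4. Could a gap of this kind produce a false signal?** Take the 320 patients left after losses and, as a further assumption, apply the MAI design effect of 1.12 to safety: 320/1.12/2 = about 143 effective patients per arm. With true risk 30% in both arms and detection 70% against 90%, recorded risks are 0.30 × 0.70 = 0.21 and 0.30 × 0.90 = 0.27. The pooled risk is 0.24, and the standard error is about 0.0505 under the null and 0.0504 under the alternative. The chance of a significant excess in the intervention arm (two-sided 5% test) is Φ[(0.06 − 1.96 × 0.0505)/0.0504] = Φ(−0.77), about 22%, against a nominal 2.5% in that direction. At true risks of 10%, 20% and 40% the same calculation gives about 9%, 15% and 30%.

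Steps 3 and 4 show how sensitive the comparison is. They do not estimate the bias in this trial.

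**The case against.** **The article is a condensed protocol.** The case report form may contain standard safety questions, and interactions may already be derived from the drug list, since active ingredient and dose are recorded for each drug. This is fair, and the absence of such detail is not the point. The point rests on what the article does fix: the outcome, the responsible person, the timing and the one-sided intervention. Table 1 assigns the safety row to the FP, and nothing in the article assigns it elsewhere.

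**Evaluation is blinded.** The Discussion says so in general terms, but Table 1 limits external evaluators to the MAI. Even a blinded classification of safety events could only sort what the unmasked FP had found and entered.

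**The direction is not shown.** This stands. A reader might infer that the comparison is necessarily biased against the intervention. The documents do not support that. An FP recording the results of his or her own intervention could under-report, and an interaction found and resolved at the first interview may be gone by T1.

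**The contact count.** A reader might also count three drug-review contacts against two and conclude that a third of the intervention-arm opportunities have no control counterpart. Table 1 schedules no safety recording at the post-randomization interview, and the count ignores ordinary usual-care visits, so it does not measure the gap. The shared T1 and T2 recordings narrow the difference without closing it.

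**Conclusion.** The point holds in a limited form. As written, the plan allows safety events to be ascertained differently in the two arms: clearly for interactions, plausibly for adverse reactions. The expected direction is against the intervention, because training and directed assessment should raise detection, but the net sign and size cannot be established from the documents. The recorded risk ratios of 0.86 to 1.60 under a true ratio of 1.00 follow from assumed detection rates and are illustrations only. It would be too strong to say that the safety objective cannot be answered; it can be answered better, at little cost. One secondary outcome is concerned. The MAI is externally rated, and its analysis and the sample size are untouched.

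**What to change.** 1. **Interactions.** In Secondary outcomes and Table 1, state that they are derived from the drug treatment plan already recorded for every patient at T0, T1 and T2, using one fixed list or tool applied to both arms by the existing blinded external evaluators, and not from FP reports. This also supplies the missing baseline value.
2. **Adverse reactions.** Count them in both arms from the same fixed questions with the same recall period at T1 and T2, asked at T1 before any intervention activity. Count every reaction reported there, whether or not it was first noted at an interview. Dropping interview-detected reactions would be a one-sided exclusion favouring the intervention. Report reactions noted only at an intervention interview separately and descriptively.
3. **Limitation.** State that reactions are still elicited by unmasked FPs, so part of the possible difference in detection remains.

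Cost: changes to protocol and case report form wording, and a little more evaluator work on data already collected; no new visits. Transient reactions not recalled at T1 or T2 leave the between-arm count.

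### Hazardous interactions are recorded by the unmasked treating physician in both arms, which may prompt medication review in controls at 6 months and leaves this outcome unblinded

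*Protocol article*

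**What the plan says.** Under Secondary outcomes, medication safety is "measured as the incidence of adverse drug reactions and potentially hazardous interactions", classified with a published taxonomy. In Table 1 (Variables) the row reads "Medication safety X X FP": the two marks stand under T1 and T2, none under T0, and the responsible entity is the FP. The two intervention rows of that table are labelled as applying to the intervention group; this row is not. The text above the table adds: "Patient data will be collected by the recruiting FP, who will also be responsible for patient follow-up". For the MAI, by contrast, Table 1 names the external evaluator and the evaluation committee.

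The Background describes the Ariadne principles as "based on a thorough assessment of the diseases, treatments and potential treatment interactions, global clinical status, and context of the patient by the physician", and the Abstract also lists potential interactions. The intervention consists of an online training course followed by the step given as "Second phase: Physician-patient interview based on the Ariadne principles". Controls are to receive usual care.

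The Discussion states that the intervention cannot be masked but that outcomes are evaluated by trained physicians and pharmacists who do not know the allocation. It lists four measures against contamination and acknowledges a Hawthorne effect.

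**The concern.** Two problems follow if the treating FP is the one who finds the interactions.

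First, the data collection may act on the control arm. A control FP who is asked at T1 to record hazardous interactions in a patient on five or more drugs has reason to look through the drug list and may change it. Looking for interactions is part of what the intervention asks of physicians. Any change would fall between T1 and T2 and would shrink the 12-month contrasts in MAI, safety and service use. Afterwards, such shrinkage could not be told apart from a waning effect of the intervention.

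Second, the ascertainment is unblinded and may differ by arm. Intervention FPs have been trained in appropriateness of prescribing and in the Ariadne principles; control FPs have not. Trained physicians may recognise and record more interactions in the same drug list, which would make the intervention look less safe. Knowing the allocation could also push recording the other way. The direction cannot be predicted.

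**Working it through.** **1. Who records, and in which arm.** The Table 1 row names the FP and carries no arm label, and the Variables text says that the recruiting FP collects patient data. Where an assessor other than the treating physician is meant, the table uses a separate code, as it does for the MAI. The natural reading is therefore the treating FP, in both arms.

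**2. How interactions are detected.** This is not stated. Judgement by the FP, prescribing software, or later coding from the submitted drug plan would all fit the text. Active detection by the control FP is an inference from who is responsible.

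**3. Overlap with the intervention.** Interaction assessment is one element of the Ariadne model, beside diseases, clinical status and context, and it leads to prioritisation and shared goals. A control FP would meet that one element without the training or the structured interview.

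**4. Existing safeguards.** The four measures in the Discussion are limited detail at the welcome session, a confidentiality agreement, reminders to the intervention group, and later training for controls. All concern information about, or access to, the intervention. None concerns exposure through the study's own data collection.

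**5. Timing.** Medication safety is not marked at T0, so controls first meet the item at T1. The primary outcome is the T1-T0 change in MAI, and the T1 drug plan belongs to the same visit. An effect on the primary outcome would require the safety item to be completed, and acted on, before the T1 drug plan is recorded. The article does not give that order.

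**6. Baseline.** The outcome is an incidence, yet Table 1 marks no T0 value. The drug plan is marked at T0, T1 and T2, and the Explanatory and adjustment variables section says that it holds active ingredient and dose.

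**7. Sensitivity only.** The planned sample size reproduces. With a difference of 2, an SD of 6, two-sided alpha 0.05 and 80% power, the t-test calculation gives 142.25, hence 143 per arm and 286 in total. DE = 1 + (5 − 1) × 0.03 = 1.12; 286 × 1.12 = 320; 320 / 0.80 = 400.

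At 160 evaluable patients per arm, the effective number per arm is 160 / 1.12 = 142.9. Then SE = 6 × √(2 / 142.9) = 0.71, and power = Φ(d / 0.71 − 1.96). The table carries the T1 difference and SD over to T2, which the article does not do, and assumes the dilution.

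| Assumed dilution | Difference d | Power |
|---|---|---|
| 0% | 2.0 | 80% |
| 5% | 1.9 | 76% |
| 10% | 1.8 | 72% |
| 20% | 1.6 | 62% |
| 30% | 1.4 | 51% |

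These figures show how a small dilution would act. They do not estimate the effect of the T1 item.

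**The case against.** The strongest reply is that the column in Table 1 says who is responsible for an item, not how it is obtained. The Discussion's statement on blinded evaluation is not limited to the MAI, so FPs might submit data that blinded evaluators then classify. A condensed article may leave such detail to the full protocol or the case report form. This stands in part: nobody can say from the article that control FPs must screen drug lists. But the article does assign the outcome to the FP, and that assignment sits badly with a general statement of blinded evaluation. The two should be reconciled.

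A reader might infer that controls stop receiving usual care from T1 onward because they receive the core of the intervention. The article does not support that. It calls the sharing of treatment goals the cornerstone, the tested package is training plus interview, and usual care is not defined as excluding attention to interactions.

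A reader might also infer a threat to the primary endpoint or a known loss of power. Neither is shown. The first depends on an unstated order within the T1 visit. The second depends on an assumed dilution at a time point for which the trial was not sized and which the Statistical analysis section calls non-confirmatory. The item is completed in both arms, so dilution also requires a larger response in controls, which is plausible but not demonstrated.

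Finally, the article already concedes dilution from physicians knowing that they are observed. That is a general effect that cannot be removed; a specific prompt on interactions can be.

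**Conclusion.** The point holds in a limited form. The article gives ascertainment of hazardous interactions to the unmasked treating FP in both arms, although interaction assessment is an element of the model under test and outcome evaluation is described as blinded. If those FPs detect the interactions themselves, two consequences follow: a possible prompt to control FPs at T1, which would bias the secondary T2 contrasts toward no difference, and unblinded ascertainment with training in one arm only, which could bias the interaction outcome in either direction. The size of both is unknown. The primary T1-T0 MAI comparison and the sample size are not called into question. The change is still worth making, because the 12-month effects on appropriateness and medication safety are named secondary objectives and the problem can be avoided with data already collected.

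**What to change.** Split the medication safety outcome. FPs in both arms continue to record adverse drug reactions. Potentially hazardous interactions are derived by the blinded evaluators who already rate the MAI, from the drug treatment plans recorded at T0, T1 and T2. Change the responsible entity in Table 1 accordingly, add T0 for the interaction part, and state the detection method under Secondary outcomes. The T0 value lets interactions already present at entry be separated from new ones.

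The cost is one amended table row, one item moved off the FP's form, and some extra coding for the existing evaluators; the article gives no workload figures from which to size that. No new patient data or visits are needed. How any hazard that comes to light is handled is a matter for the sponsor's own safety procedures and is not part of this recommendation. If detection is already done by software or by blinded evaluators, stating that in the article and correcting the table would be enough.

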### Explanatory and adjustment variables

#### Patient (first level) variables

Socio-demographics: age, sex, nationality, AC of residence, marital status, socioeconomic status (monthly salary expressed as multiples of the minimum wage), family composition (number of people living at home), housing indicators, social support (Dukes-UNC-11 questionnaire adapted to Spanish [43]), profession, and social class [44].Morbidity: number and description of chronic diseases based on the International Classification of Diseases in PC (ICPC).Pharmacotherapeutic treatment plan: number and type of drugs prescribed, active ingredient, and dose of each drug.

#### FP (second level) variables

Socio-demographics: age, sex.Professional performance: years of professional experience, tutor of residents (yes/no), average workload measured as the average number of daily consultations per FP during the year previous to the start of the study.Prior training: in polypharmacy, multimorbidity, and/or shared decision making.

### Statistical analysis

All analyses will be carried out in accordance with the intention-to-treat principle, with significance set at *p* < 0.05.

Description of baseline characteristics (qualitative and quantitative variables) of patients and professionals for each arm of the study, with corresponding 95% confidence interval (95% CI). Description of patients that abandon the study, including patient characteristics and reasons for loss during follow-up.

Basal comparison between groups using statistical tests for independent samples (Student’s *t* test or chi-square test). Tests for related samples (ANOVA for repeated measures) will be used to analyse changes within groups and between visits.

Analysis of main effectiveness: between-group difference in T1-T0 MAI score, with corresponding 95% CI. Multilevel analysis will be used to adjust models. Difference in MAI score will be considered the dependent variable; baseline patient (first level) and FP (second level) variables and treatment arm will be considered fixed-effect independent variables; and grouping by FP will be considered a random factor. Missing data pertaining to professionals and/or patients will be addressed by replacing missing values with the most recent available or baseline data.

Analysis of secondary effectiveness (non-confirmatory): between-group difference in means or proportions of T2-T0 MAI score will be determined using the appropriate statistical tests and an explanatory model will be adjusted using the same methodology applied to the main outcome variable.

Estimated quality-adjusted life years (QALYs) gained at the population level, with corresponding 95% CI, as determined using parametric methods and bootstrap techniques. Given the 1-year time horizon, no discount rates will be applied.

Calculation of cost-utility ratio: this is an exploratory objective for which a specific design has not been applied. The cost-utility ratio will be estimated by dividing the total cost by the sum of the potential gains expressed in QALYs. A multivariate sensitivity analysis will be performed in which costs will oscillate within the range of uncertainty of a normal distribution. The benefits (QALYs) will also oscillate within the same range.

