### Sample size

The sample size was calculated under the hypothesis that the intervention would lead to a difference of at least 2 units in the change in MAI score at 6 months (T1 vs T0) (i.e. a clinically relevant difference) between study groups. Differences in MAI are assumed to be normally distributed in each intervention arm and the variances are assumed to be equal. According to previous studies, the standard deviation of the difference in MAI is 6 units [32–34]. Therefore, the study should be capable of detecting an effect size of 0.3 (2/6). Considering a power of 80% and assuming simple random sampling, the required sample size would be 286 patients (143 patients in the intervention group and 143 in the control group).

The effective sample size in this type of study design depends on the average size of the cluster and the degree of correlation between individuals in the cluster. Accordingly, it is necessary to adjust the calculated sample size in accordance with the design effect (DE). An average cluster size of 5 patients per FP and an intraclass correlation coefficient of 0.03 [35] produces the following (DE = 1 + (5 − 1) × 0.03 = 1.12) which gives a sample size, corrected for the DE, of 320 patients. Assuming a percentage of losses of 20%, the final sample size required is 400 patients (200 per group). Assuming that each FP will recruit 5 patients, 80 FPs (40 per group) will be required. In each AC, 133 patients will be recruited.

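### The t, chi-square and repeated-measures ANOVA tests named for patient data ignore clustering by family physician, and the plan does not fix which estimate is the primary result

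*Protocol article*

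**What the plan says.** The Randomization section makes the FP the unit of randomisation and the patient the unit of analysis. The Sample size section accepts what follows from this: "it is necessary to adjust the calculated sample size in accordance with the design effect (DE"). It takes 5 patients per FP and an ICC of 0.03, which gives 1.12.

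The Statistical analysis section sets the threshold for all analyses "with significance set at *p* < 0.05" and then names these methods:

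- Baseline: "Basal comparison between groups using statistical tests for independent samples", with Student's t or chi-square as the tests.
- Change over time: "Tests for related samples (ANOVA for repeated measures) will be used to analyse changes within groups and between visits".
- Main effectiveness: "between-group difference in T1-T0 MAI score, with corresponding 95% CI. Multilevel analysis will be used to adjust models". The model that follows has the MAI difference as outcome, arm and baseline patient and FP variables as fixed effects, and FP as a random factor.
- T2-T0 MAI, labelled non-confirmatory: unspecified suitable tests, plus a model built as for the main outcome.

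The Abstract follows the same order for the primary outcome: the MAI difference with its interval first, then multilevel analysis for confounding.

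**The concern.** Patients of one FP share a prescriber, so their prescribing outcomes are expected to be correlated. The sample size allows for this, but the tests named for patient-level baseline variables and for change do not. A t or chi-square test for independent samples has no place for FP. Repeated-measures ANOVA deals with the correlation between visits of one patient, but not with the correlation between patients of one FP. Standard errors from these tests come out too small and p-values too low.

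The baseline p-values also serve little purpose. FPs are randomised only after patients have been selected and baseline data collected, so a baseline difference between the arms is a chance difference.

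The second issue is the primary result. The main-effectiveness paragraph can be read as one analysis (an estimand, then the model that estimates it) or as two (an unadjusted difference with its interval, then an adjusted one). If there are two, no sentence says which decides. That leaves room to choose once both are known.

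**Working it through.** **Inputs.** From the Sample size section: "a difference of at least 2 units in the change in MAI score at 6 months"; "the standard deviation of the difference in MAI is 6 units"; "Considering a power of 80% and assuming simple random sampling"; 5 patients per FP; ICC 0.03; 20% losses; 40 FPs per group. From the Statistical analysis section: significance level 0.05. Sidedness is not stated. Two-sided is assumed because it reproduces the planned number.

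**Step 1. Reproduce the plan's sample size.**

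- Normal approximation: n per arm = 2 × 6² × (1.960 + 0.842)² / 2² = 141.3, so 142. The t-based solution is 142.2, so 143, as stated (286 in total).
- Design effect: DE = 1 + (5 − 1) × 0.03 = 1.12, and 286 × 1.12 = 320.3, stated as 320.
- Losses: 320 / 0.80 = 400, as stated.

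The plan's figures reproduce, so DE 1.12 is a fair measure of the clustering that the plan itself expects.

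**Step 2. Effect of leaving FP out of a test on patient data.** The correct standard error is √DE times the naive one, so:

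- understatement of the standard error = 1 − 1/√DE
- true type I error of a nominal 5% test = 2 × [1 − Φ(1.96/√DE)]

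At DE 1.12, √DE = 1.058. The understatement is 1 − 1/1.058 = 5.5%. The type I error is 2 × [1 − Φ(1.852)] = 6.4%, so a naive 95% interval covers 93.6%.

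| Patients per FP | ICC | DE | SE too small by | Type I error |
|---|---|---|---|---|
| 5 | 0.03 (plan) | 1.12 | 5.5% | 6.4% |
| 4 (after 20% losses) | 0.03 (plan) | 1.09 | 4.2% | 6.0% |
| 5 | 0.01 (assumed) | 1.04 | 1.9% | 5.5% |
| 5 | 0.05 (assumed) | 1.20 | 8.7% | 7.4% |
| 5 | 0.10 (assumed) | 1.40 | 15.5% | 9.8% |

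**Step 3. Check by simulation.** With 40 FPs per arm, 5 patients each, ICC 0.03 and 40,000 replicates under the null, the independent-sample t test rejected in 6.3% of replicates. A paired test of change within one arm, standing in for the within-group analysis, rejected in 6.4%. A t test on FP means, which respects the clusters, rejected in 4.9%.

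**Step 4. What it would mean for the primary interval, if it ignored FP.** The documents do not say that it does. With SD 6 and 320 patients analysed, the naive standard error is 6 × √(4/320) = 0.671, a 95% half-width of 1.31 MAI units. With DE 1.12 it is 0.671 × 1.058 = 0.710, a half-width of 1.39.

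**The case against.** The strongest reply is that the analysis that matters is already clustered. In the main-effectiveness paragraph the only method named is a multilevel model with FP as a random factor, and no t test is assigned to the primary outcome. A reader might infer from the order of the sentences that the trial has a second, cluster-ignoring primary result with an interval that is too narrow. The text does not support that. It leaves open whether a separate unadjusted difference exists and does not say how its interval would be computed. This part of the objection stands, and the primary point is limited to ambiguity.

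A reader might also infer that spurious baseline imbalances would decide the adjustment set. The documents give no such rule. The patient and FP adjustment variables are listed in advance, and the Discussion commits to adjusting for prior training without making this depend on a baseline test.

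Three further points stand in part:

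- Independent-sample tests are valid for FP characteristics, where each FP contributes one record. The criticism covers patient variables only.
- The repeated-measures ANOVA is not presented as the test of the intervention. It still reports p-values whose errors ignore FP. The Discussion itself expects that observed FPs in both arms may change their prescribing, so within-arm change says little about the intervention.
- The T2-T0 model follows the main model and so carries the FP factor. Only the accompanying unspecified test is left without a stated allowance for clustering.

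None of this answers the narrower point. The article chose these tests by name, and as written they contradict its own design effect.

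**Conclusion.** The point holds in two limited parts.

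First, the t, chi-square and repeated-measures ANOVA tests on patient variables are inconsistent with the cluster design. At the plan's own inputs the standard error is about 5.5% too small and the type I error about 6.4% instead of 5%. The inflation is modest, and it falls on baseline and within-arm comparisons, not demonstrably on the effectiveness result. The size rests on a two-sided 5% level, equal cluster sizes, and the sample-size ICC applying to the variable tested. The figures of 7.4% and 9.8% rest on ICCs that are not in the documents.

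Second, the article does not fix whether an unadjusted T1-T0 difference is reported beside the multilevel estimate, or which of them decides the trial. This is a gap in specification, not a demonstrated error in the primary interval. Both parts should be corrected, because correction costs almost nothing and removes a choice that could otherwise be made after the results are known.

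**What to change.** - Name the treatment-arm coefficient and its 95% CI from the multilevel model with FP random intercept as the single primary result.
- If an unadjusted difference is wanted, compute it from a model with arm and FP random intercept only, and label it supportive.
- Describe patient baseline characteristics by arm without p-values.
- Replace the repeated-measures ANOVA with a mixed model with arm, visit and their interaction, and random effects for FP and patient. Report the between-arm contrasts at T1 and T2.
- State that the T2-T0 between-group comparison also allows for FP clustering.

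The changes are to the wording of the protocol and the analysis plan. No further data or patients are needed. Intervals become slightly wider (by a factor of 1.058 at DE 1.12 wherever clustering would have been ignored), and the mixed models take a little more work than the tests they replace.
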